## Abstract

**Background:**

Preeclampsia is 1 of the 3 leading causes of maternal mortality worldwide. Unfortunately, its exact pathogenesis is still unclear. Published metabolomic and gene expression analyses point to coenzyme A (CoA) restriction in the placenta as a factor underpinning the observed complications of preeclampsia, but this hypothesis has never been tested.

**Objective:**

This pilot study aims to discover evidence supporting the CoA-restriction hypothesis through 2 avenues. The first of these involves developing a procedure for the quantitative determination of metabolites to discover if harmful metabolites are elevated in patients with preeclampsia, while the second seeks to emulate the onset of CoA restriction in cultured cells.

**Methods:**

This manuscript provides a rationale and a protocol for a clinical study and laboratory experiments to test the hypothesis. The methods have 3 key aspects. Phase 1 comprises optimization of assays of 5 key metabolites arising from CoA restriction, namely L-leucine, ketoisovalerate, ketodeoxycholate, oleic acid, and sphingosine-1-phosphate. Phase 2 comprises recruitment of patients to obtain serum samples to measure the metabolites, and phase 3 comprises culturing and treating trophoblast cells to induce CoA restriction and test the effects of the metabolites on the cells. Patients with preeclampsia and healthy controls will be recruited based on World Health Organization criteria for preeclampsia. Exclusion criteria include multiple pregnancies, premature rupture of membranes, and various medical complications. Blood samples will be collected and analyzed using high-performance liquid chromatography/mass spectrometry (HPLC/MS) to quantify key metabolites associated with CoA restriction. For trophoblast cell studies, BeWo cells will be cultured under conditions likely to induce CoA restriction, including hypoxia and human chorionic gonadotropin supplementation, and will also be treated with the key metabolites to determine what effect they might have. Cell viability, apoptosis, energy metabolism, and gene expression (focusing on genes involved in CoA synthesis and metabolism) will be assessed. Statistical analysis will involve 2-tailed *t* tests or Mann-Whitney *U* tests to compare metabolite concentrations between patients with preeclampsia and controls. A correlation matrix will be used to explore associations between metabolite levels and patient characteristics.

**Results:**

Institutional review board ethics approval has been obtained for this study. Patient recruitment started April 1, 2025. The 5 metabolites have been purchased in synthetic form and used to optimize the HPLC/MS assays in preparation for receiving blood samples. The trophoblast cell-line culture is being optimized.

**Conclusions:**

The findings of this study will demonstrate that key metabolite concentrations can be quantified using HPLC/MS and indicate if CoA restriction is associated with preeclampsia. If so, this provides a significant, novel avenue for research into the treatment and prevention of the disease.

**International Registered Report Identifier (IRRID):**

PRR1-10.2196/66202

## Introduction

### Background

Preeclampsia is a major pregnancy-related disorder that affects approximately 3% to 10% of pregnancies worldwide [1], and it is also 1 of the 3 leading causes of maternal morbidity and mortality [2]. Women affected by preeclampsia usually present with new-onset hypertension and proteinuria developing during the second half of pregnancy, though presentation can vary. In severe cases, organ damage to the kidney and liver occurs, with hematological involvement and, if left to progress, women will experience neurological complications including seizures or eclamptic fits [3,4]. The babies of women with preeclampsia are at increased risk of intrauterine growth retardation, placental abruption, preterm rupture of membranes, premature delivery, and death [5]. It is therefore important to further investigate the pathophysiology of preeclampsia and potential drug targets, with the aim of reducing maternal mortality and morbidity worldwide.

Unfortunately, the exact pathogenesis of preeclampsia is still unclear, although it is generally thought that dysfunction of the maternal endothelium caused by systemic inflammation and oxidative stress plays a critical role in the development and progression of the disease [6]. A multiomics analysis of 7 untargeted studies has shown that a reduced level of placental coenzyme A (CoA) explains the change in concentration of at least half (26/51) of perturbed plasma metabolites in the first trimester of women who go on to be affected by preeclampsia [3]. Also, gene-expression changes indicate a reduced ability to synthesize CoA from vitamin B5, reduced expression of genes for enzymes consuming free cytosolic CoA, and elevated expression of enzymes releasing CoA from thioesters [3]. CoA is a fundamental carrier of acyl groups in many metabolic pathways that are critical for the cellular reactions involved in energy metabolism and branched-chain amino acid degradation [3]. Therefore, any disruption in the synthesis of this essential cofactor can lead to a disruption in energy metabolism and have significant physiological consequences, including preeclampsia.

### Perturbed Metabolites

In this context, CoA restriction leads to elevated levels of potentially harmful metabolites, even in the first trimester. These include dietary unsaturated fatty acids, sphingosine-1-phosphate, branched-chain amino acids and their keto acids, and ketodeoxycholates (Figure 1) [7]. Unsaturated fatty acids, including oleic acid, bind to peroxisome proliferator activator receptor α (PPARα), promoting peroxisome formation. Transcriptomic data reveals elevated expression of genes for peroxisomal proteins. Particularly under CoA restriction, this can explain the known oxidative stress observed in preeclampsia. Depending on the receptors to which it binds, sphingosine-1-phosphate exerts various physiological effects, including cell survival, angiogenesis, vasoconstriction (inducing hypertension), macrophage recruitment, inflammation, and programmed cell death [8].

**Figure 1 figure1:**
[figure not shown]
Clinical consequences of placental coenzyme A (CoA) restriction. Text in blue, red, black, and purple respectively denotes reduced concentrations, elevated concentrations, physiological conditions, and pathological states. Red and blue arrows respectively represent increased and decreased molecular concentrations. Black arrows depict the chains of consequence leading to disease states. The dashed lines separate different areas of metabolism. Pantothenate kinase 1 (PANK1) is the initial and regulatory enzyme in CoA synthesis from vitamin B5. This leads to elevated levels of unsaturated fatty acids, sphingosine-1-phosphate, and interruption of branched-chain aliphatic amino acid degradation. PPARα: peroxisome proliferator activator receptor α.

The plasma levels of 6 amino acids are significantly elevated, including the branched chain amino acids valine, isoleucine, and leucine [3]. The latter can cause insulin resistance by blocking signaling via the mammalian target of rapamycin complex 1 (mTORC1), providing an explanation for the sometimes-observed elevated glucose level and possibly contributing to the proteinuria typical of preeclampsia. The equivalent ketoacids of these amino acids, as well as some of their intermediate degradation products, are elevated (indicative of CoA restriction) and are known to cause mitochondrial stress, acidosis, and neurotoxicity, especially 2-oxomethyl butanoic acid (also known as ketoisovaleric acid), 3-hydroxyisovaleric acid, and 3-hydroxybutanoic acid. Ketodeoxycholates are secreted from and recycled by the liver to disrupt ingested membranes. At high enough levels in plasma, they can disrupt the cell membranes of many organs, including the kidney (leading to proteinuria), blood cells, and the liver (contributing to hemolysis, elevated liver enzymes, and low platelets syndrome [HELLP]). The past multiomics study mentioned above also identified adverse positive-regulatory feedback loops [3]. In placental cells, they can cause a progressive increase in the concentration of the harmful metabolites that ultimately causes preeclampsia. Finally, it should also be noted that oleic acid, sphingosine-1-phosphate, and ketoisovaleric acid are also members of a predictive biomarker set for preeclampsia [7].

### Placental Gene Expression Changes in Preeclampsia

A meta-analysis [9] revealed that the expression of over 7600 genes in the placenta is altered in preeclampsia. To test the hypothesis of CoA deficiency, the present study will focus on genes influencing the synthesis pathway of CoA and the above metabolites, as well as on insulin resistance. The pantothenate kinase 1 (PANK1) gene, whose transcription levels are low, and even lower in preeclampsia, encodes the crucial first step in CoA synthesis. Programmed cell death is thought to repress PANK1, which at this early stage is probably due to hypoxia. However, expression of the gene for the final step of CoA synthesis, dephospho-CoA kinase (DCAKD), is elevated. In preeclampsia, lipoprotein lipase (LPL) gene expression is elevated, which increases the release of fatty acids from chylomicrons, including oleic acid. The initial step in the pathway to sphingosine-1-phosphate is catalyzed by serine palmitoyl transferase, whose activity is increased by the elevated expression of its activator (serine palmitoyltransferase small subunit A [SPTSSA]).

Branched-chain amino acids are usually degraded within mitochondria. However, in preeclampsia, the placenta also overexpresses the gene for cytosolic branched-chain amino-transferase 1 (BCAT1), allowing ketoisovalerate to be produced even in the cytosol. In mitochondria, the next step of branched-chain amino-acid degradation is impeded by the elevated expression of an inactivating protein kinase (branched-chain ketoacid dehydrogenase kinase; BCKDK), whose expression should otherwise be repressed by the activated PPARα. Finally, the expression of phosphatidyl choline transfer protein (PCTP) is elevated to enable free fatty acids to enter mitochondria, but this protein also blocks insulin signaling via mTORC1, and it is of interest for this reason.

### Trophoblast Biology

Preeclampsia can occur in the absence of a fetus but in the presence of trophoblast tissue with hydatidiform moles [10], indicating a crucial role for trophoblasts. Indeed, trophoblasts play a principal role in placental development [11]. Their cell lineage begins with cytotrophoblasts, which are the initial stem cells that proliferate in the first and second trimesters and go on to form daughter cells with defined roles. Those in the cell column first specialize into extravillous trophoblasts, from which 2 further cell types arise. Interstitial extravillous trophoblasts anchor the growing placenta to the uterus, while endovascular extravillous trophoblasts invade the maternal spiral arteries, replacing the endothelial lining to allow low-pressure perfusion of maternal blood through a lumen to the maternal veins.

This lumen is filled with chorionic villi, providing a very large surface area permitting exchange of gases and biochemicals between the maternal and fetal vascular systems. These villi have two cell layers. Cytotrophoblasts line the layer next to the fetal blood, while multinucleated syncytiotrophoblasts coat the surface next to the maternal blood. The latter are formed by trophoblast-cell fusion, which is promoted by human chorionic gonadotrophin (hCG) and insulin-like growth factors [12,13].

Trophoblasts have been grown in cell culture for 60 years. Apart from primary cell cultures and immortalized cell lines, there are also several gestational choriocarcinoma cell lines [14]. Of the latter, BeWo cells are derived from a cytotrophoblast and widely used as a model because they can also fuse to form a syncytium [15]. A recent transcriptomic comparison of cell lines indicated that none were very similar to various trophoblasts extracted by cell sorting, though BeWo cells were the closest [14]. However, a study focusing on a subset of preeclampsia markers showed that a BeWo-hypoxia model mimics a key pathogenic mechanism of preeclampsia [16]. Programmed cell death plays a critical role in embryonic implantation and placental development, but hypoxia and/or oxidative stress are thought to cause early aberrant trophoblastic cell death [17] that eventually results in preeclampsia.

### Aims of This Study

Prior work indicates that CoA levels are reduced in the first trimester of pregnancies, triggering the rise of harmful metabolites that later cause preeclampsia. It is extremely difficult to test this hypothesis by direct measurement of CoA concentration, because it is bound to many different metabolites and proteins, and obtaining a biopsy from the diseased part of a placenta would be difficult and highly invasive. However, the metabolites generated as a consequence of CoA restriction are readily detected using mass spectroscopy, even though they are a mixture of hydrophilic and hydrophobic molecules. Hence, this pilot study aims to uncover evidence supporting the CoA restriction hypothesis through 2 avenues. The first of these is to provide the proof of concept of a methodology to quantify the metabolites (specified in Figure 1) and then compare the levels in patients with preeclampsia versus matched controls. The second seeks to emulate the onset of CoA restriction in cultured cells.

Hence, this article outlines a 3-phase protocol (protocol version 1.1, May 23, 2024) for clinical samples and cell culture studies to screen for the indirect effects of CoA restriction (Figure 2). Initially, laboratory methods will be developed to quantify levels of the harmful metabolites in serum. Then, blood samples from patients with preeclampsia and matched controls will be taken to determine if the predicted harmful metabolites are elevated in patients with the disease. In parallel, trophoblast cells will be stressed to induce CoA restriction, and then investigated in 3 ways. The first will determine if the harmful metabolites appear in the cell culture medium, while the second will study the effect of these metabolites on otherwise healthy cells and the third will determine the expression level of genes known to be affected by the disease (ie, those described in the Placental Gene Expression Changes in Preeclampsia section) to determine if they have significantly changed.

**Figure 2 figure2:**
[figure not shown]
Flow of materials and data through the CoA restriction study. The in vivo and in vitro components are demarcated by the dashed line. The top row of boxes indicates the control and disease or stressed material that is fed into the middle blocks, denoting laboratory techniques. The output data from these assays are then subject to statistical analysis to identify significant changes. Cell status refers to assays of cytotoxicity, apoptosis, and energy metabolism. HPLC/MS: high performance liquid chromatography/mass spectrometry; PE: preeclampsia; qPCR: quantitative polymerase chain reaction.

## Methods

### Objectives

This study has 3 objectives: first, develop a set of targeted high performance liquid chromatography/mass spectrometry (HPLC/MS) assays to accurately quantify the concentration of key harmful metabolites in patient blood samples and cell culture media; second, use this set of targeted assays to measure harmful metabolite concentrations in patients with preeclampsia and compare them with healthy controls to determine if they are elevated in preeclampsia; and third, subject the cultured trophoblasts to hypoxia and the harmful metabolites to determine what conditions initiate CoA restriction.

After completion of objective 1, the flow of materials, laboratory investigation, and data analyses will follow the paths outlined in Figure 2.

### Development of Targeted Metabolomic Assays

Oleic acid (Sigma 05508), sphingosine-1-phosphate (Sigma 860492P), L-leucine (Sigma L8000), 3-methyl-2-oxobutyrate (Sigma 198994), and 12-ketodeoxycholic acid (Sigma SMB00913) have been purchased from Sigma Chemical Co. Pure compounds are solubilized and analyzed by direct infusion into an Orbitrap Exploris 480 mass spectrometer (Thermo Fisher Scientific Inc), the abundant intact precursor mass adducts are identified, and the collision energy is optimized for tandem mass spectrometry profiling. The compounds are then diluted in 0.1% formic acid and injected across a 15-cm C18 column to determine their retention time. The resulting precursor-fragment transitions and retention time boundaries thus constitute the specific assays for each metabolite.

The metabolite extraction procedure and absolute quantification limits are then optimized by spiking the metabolite standards into and then extracting them from the commercially available National Institute of Standards and Technology standard plasma matrix.

### Recruitment

Women with preeclampsia will be identified by the obstetricians collaborating with the study from the antenatal clinics and wards at Latifa Hospital in Dubai. Women with preeclampsia who meet the inclusion criteria outlined below will be approached verbally, asking if they would like to participate in this study. A patient information sheet will be provided, and after they provide written informed consent, they will be recruited into the study.

Baseline clinical and laboratory characteristics will be collected from the patients’ medical notes, including obstetric history, booking weight, height, renal and liver function, comorbidities, and smoking history. A data collection form has been designed for this purpose (Multimedia Appendix 1). The collected data will be anonymized and linked to samples by study ID only. Concurrent control participants will be identified following a review of the antenatal clinic lists to seek women with uncomplicated pregnancies who are undergoing routine antenatal care in the same antenatal clinic at Latifa Hospital in Dubai. Controls will be matched for approximate weight, age (5-year age group) and week of gestation. Control participants who meet the inclusion criteria outlined below will also be approached verbally, asking if they would like to participate in this study.

Patient blood samples will be taken at the time of routine phlebotomy for blood tests required as part of clinical care. As such, no adverse events specifically related to the study procedure are anticipated.

Blood samples will be collected in a heparinized EDTA (ethylenediaminetetraacetic acid) 10-ml container and transported immediately on ice to the laboratory for processing, as described in Blood Metabolite Analysis section below. One member of the research team has the responsibility for sample processing to ensure consistency. Metabolite measurements will be conducted by 2 members of the research team.

Preeclampsia will be defined as per the WHO Recommendations for Prevention and Treatment of Pre-eclampsia and Eclampsia [18]; specifically, the onset of a new episode of hypertension during pregnancy, characterized by persistent hypertension (diastolic blood pressure ≥90 mm Hg), and substantial proteinuria (>0.3 g/24 hours or more or a protein level of +2 or above in the urine dipstick test). The gestational week in which the sample is collected will be recorded for all women.

The exclusion criteria will include multiple pregnancy (eg, twins or higher-order gestations), premature rupture of the membranes; chorioamnionitis; oligohydramnios; fetal growth restriction; polyhydramnios; fetal anomalies; local or systemic diseases; tobacco use; and medical complications, including autoimmune disorders (antiphospholipid syndrome, systemic lupus erythematosus, hemolytic uremic syndrome, acute fatty liver of pregnancy, thrombotic thrombocytopenic purpura, and pheochromocytoma); hematologic disease; neurologic disorders; gestational hypertension; hereditary or acquired antithrombin III deficiency; connective tissue disease; diabetes mellitus; chronic hypertension; inflammation; and chronic renal diseases, as well as regular treatment within the last 3 months with aspirin, antihypertensive drugs, nonsteroidal anti-inflammatory drugs, or antibiotics [19].

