### Power

This prospective, cross-sectional, case-control study will include 40 pregnant women, with 20 women diagnosed with, followed up on, and treated for preeclampsia at Latifa Hospital in Dubai, and 20 women (matched for approximate weight, age [5-year age group], type of pregnancy [single or multiple], and week of gestation) with normal pregnancies. This is about half the numbers in previous metabolomic studies of preeclampsia but should be sufficient to produce the variability required given that matched controls are involved. If not, this pilot study will provide the data to carry out a sample-size calculation for a future larger clinical study. The analysis of data from this study will be primarily focused on descriptive statistics and estimates of precision to inform a planned larger validation study. The proposed sample size in our study is also consistent with the findings from a study on the target sample sizes set for pilot and feasibility randomized controlled trials in the United Kingdom [28].

For the HPLC/MS metabolite measurement, assuming a coefficient of variance of 30%, which corresponds to several multiples of observed technical variation, power calculations indicate this study will be 80% powered to detect changes of 27%. The minimum detectable effect size was calculated using G*Power [29,30].

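### Controls are defined by an uncomplicated pregnancy at recruitment and no confirmation at delivery is stated, so women who later develop preeclampsia could modestly dilute the comparison

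*Protocol article*

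**What the plan says.** The Recruitment section identifies concurrent controls by a "review of the antenatal clinic lists to seek women with uncomplicated pregnancies who are undergoing routine antenatal care". It adds that "Controls will be matched for approximate weight, age (5-year age group) and week of gestation". Timing and data are also fixed there: "Patient blood samples will be taken at the time of routine phlebotomy for blood tests required as part of clinical care", and "Baseline clinical and laboratory characteristics will be collected from the patients’ medical notes". On the data themselves it says "A data collection form has been designed for this purpose (Multimedia Appendix 1"); the content of that form is not shown.

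The Power section opens "This prospective, cross-sectional, case-control study will include 40 pregnant women". It describes the 20 controls as having normal pregnancies, and it mentions follow-up only for the 20 cases.

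The Aims section states the hypothesis as "CoA levels are reduced in the first trimester of pregnancies, triggering the rise of harmful metabolites that later cause preeclampsia". The Perturbed Metabolites section likewise places raised levels as early as the first trimester, and adds that feedback loops push the concentrations up progressively until disease results. The Background gives the frequency of preeclampsia: it "affects approximately 3% to 10% of pregnancies worldwide".

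**The concern.** Whether a pregnancy is uncomplicated on the day a clinic list is read is a different fact from whether it was normal to the end. The article fixes the first and labels the women by the second. It states no step linking the two, and the Limitations section does not mention the gap.

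In many case-control studies this would hardly matter. Here the hypothesis puts the metabolic disturbance before the symptoms. A control sampled in mid-pregnancy who develops preeclampsia weeks later would, on the authors' account, already be on the rising path when her blood was drawn. She would raise the control mean and widen the control spread. Because controls are matched on week of gestation, those matched to the earliest cases have the longest time left in which to convert.

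The bias runs toward no difference. It would shrink the contrast for each of the five target metabolites and place mislabelled women in the discriminant analysis of the untargeted data. It would also carry a diluted effect size into the sample-size calculation that the Power and Limitations sections name as a use of this pilot.

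**Working it through.** **Inputs from the article**
- 20 cases and 20 controls; coefficient of variation 30%; 80% power for a 27% change (Power).
- Two-tailed t tests (Data and Statistical Analysis).
- Preeclampsia in 3% to 10% of pregnancies (Background), used here only as an upper range for later conversion among controls.

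**Assumptions**
- Alpha 0.05 (not stated in the article).
- p = proportion of controls who convert. A value of 1.5% is added to illustrate a lower residual risk.
- h = share of the full case shift that a converter already carries at sampling. h = 1 is the extreme; h = 0.5 illustrates a partial rise.

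**Step 1. The plan's own figure.** For an unpaired two-sided t test with 20 per group, SD 30 and the noncentral t distribution, power at a difference of 27 is 79.2%. The difference giving 80% power is 27.3. The stated 27% is reproduced, and 27.3 (power 80.1%) is the starting point below.

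**Step 2. How many converters.** Expected number = 20p. Chance of at least one = 1 − (1 − p)^20.
- p = 1.5%: 0.3 expected; 1 − 0.985^20 = 26%
- p = 3%: 0.6 expected; 1 − 0.97^20 = 46%
- p = 10%: 2.0 expected; 1 − 0.90^20 = 88%

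**Step 3. Dilution and power.** Observed difference = 27.3 × (1 − hp). Control variance = 30² + p(1 − p)(27.3h)². The SD used is the square root of the mean of the case variance (900) and the control variance.

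| p | h | Observed difference | Control variance | Power |
|---|---|---|---|---|
| 0 | – | 27.3 | 900 | 80.1% |
| 1.5% | 1 | 26.9 | 911 | 78.6% |
| 3% | 1 | 26.5 | 922 | 77.2% |
| 10% | 1 | 24.6 | 967 | 69.8% |
| 1.5% | 0.5 | 27.1 | 903 | 79.4% |
| 3% | 0.5 | 26.9 | 905 | 78.8% |
| 10% | 0.5 | 25.9 | 917 | 75.5% |

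Example, p = 10% and h = 1: difference 27.3 × 0.90 = 24.6; variance 900 + 0.10 × 0.90 × 27.3² = 900 + 67 = 967.

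**Step 4. Carry-over to the larger study.** Required sample size varies with 1/difference². At full shift the inflation is 1/0.97² = 1.06 (p = 3%) to 1/0.90² = 1.23 (p = 10%). At half shift it is 1/0.985² = 1.03 to 1/0.95² = 1.11. Added variance is ignored here.

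**Step 5. What dropping pairs would cost.** With no converters left, a difference of 27.3 has 77.9% power at 19 v 19 and 75.6% at 18 v 18. At half shift, keeping one converter in 20 (p = 5%) gives 77.9%, and keeping two (p = 10%) gives 75.5%. Dropping pairs then recovers essentially nothing. At full shift with p = 5%, dropping one pair moves power from 75.1% to 77.9%.

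**The case against.** **The silence proves little.** A reader might infer that control outcomes are never checked. The article does not say so. It condenses a full protocol (version 1.1), and its data collection form is not shown and may contain a delivery field. This objection stands: the supportable statement is that no check and no rule for converters is stated. What remains is that the article defines control status at recruitment and then calls the pregnancies normal. A delivery field alone would not settle how a converter is analysed.

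**A converter need not look like a case.** A reader might also infer from the hypothesis that her sample is already at case level. The Perturbed Metabolites section describes a progressive increase, and the Discussion expects cases to be raised far enough to explain symptoms. A woman still free of symptoms would therefore be partly raised. This stands, and the full-shift rows are an upper bound.

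**The conversion range is too high.** The 3% to 10% covers whole pregnancies in general populations. Controls are still uncomplicated at the gestational week of a woman who already has the disease, and they pass exclusions for diabetes, chronic and gestational hypertension, renal disease and autoimmune disease. This also stands.

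**The design is defensible.** The second objective asks whether metabolites are raised in preeclampsia. Comparing current disease with current non-disease at the same week is an accepted scheme that need not condition on later outcome. This is a good reason to keep the all-controls analysis. It is not a reason to leave the other contrast, against pregnancies that stayed free of the disease, unexamined when the hypothesis makes it relevant.

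**The bias is conservative.** It does not manufacture a difference where none exists. That is true, but a diluted estimate still matters in a pilot meant to supply effect and variance estimates.

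**Conclusion.** The point holds as a minor one, with moderate confidence. Controls are defined only by their state at recruitment, no confirmation at delivery is stated, and the study's own hypothesis makes later converters a source of dilution.

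The loss is at most about 3 to 10 percentage points of power, under whole-pregnancy risk and a full case shift. More plausible settings (1.5% conversion, or half the shift) cost about 1 to 5 points. These figures rest on an assumed two-sided alpha of 0.05, the unpaired t test and the plan's 30% coefficient of variation. The conversion rate and the size of the shift before onset are assumptions, not figures the article gives for these controls.

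The documents do not support the readings that outcomes definitely go unchecked, that converters are already indistinguishable from cases, or that the comparison is invalidated.

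**What to change.** In Recruitment, add that the two team members who hold the ID code (Ethical Considerations) check each control's delivery record for later preeclampsia or gestational hypertension before the dataset is locked.

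In Data and Statistical Analysis, state that the case-control differences, and the variance and effect estimates passed to the larger study, are reported twice: with all controls, and again without converters (and without their matched cases in paired tests). Show converters' values separately and give the number of women whose outcome is unknown, for example because they delivered elsewhere.

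Do not remove controls for other complications that arise later unless the same rule applies to cases. A one-sided filter would select unusually healthy controls and could bias the contrast away from zero. If the full protocol or data form already provides for the check, the article need only say so and add the analysis rule.

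The cost is one review of 20 charts with no extra visit or sample, a possible wait for the last control to deliver (the Results section expects initial results by June 2026), and a slightly smaller sample in the second analysis.
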